#### **15.3. Intensity Assignment**

583 For all observed AEs, the investigator will use the following definitions to classify  
584 the intensity of any AR recorded during the study in the CRF:

- 585       · **Mild:** Does not cause limitations in daily activities.
- 586       · **Moderate:** Causes some limitation in performing daily activities.
- 587       · **Severe:** Prevents the performance of daily activities.

#### 588 **15.4. Expectedness Assessment**

589 An AE or AR is considered unexpected if the experience (in terms of nature,  
590 severity, or frequency) is not described in the reference document for the  
591 investigational product, which in this case is TMS.

#### 592 **15.5. Procedure for AE Recording**

593 The recording of AEs must be carried out by the study's investigative team. The  
594 investigator will systematically monitor and document all reported adverse events  
595 in the clinical records, whether spontaneously reported by the patient or identified  
596 during study visits. This monitoring will occur from randomization until the final  
597 follow-up visit for each subject.

598 Only ARs and all SAEs/SARs will be recorded in the CRF for each subject. For these  
599 events, the investigator must specify the start date, causality, intensity, severity,  
600 treatment, and outcome. If treatment is administered for any of these events, it  
601 must also be recorded in the CRF.

602 All AEs will be followed until resolution, stabilization, or determination that the  
603 investigational treatment or participation in the study was not the cause. Likewise,  
604 follow-up will be conducted for any AEs persisting after the study has concluded  
605 until their final outcome is determined.

606 Analytical abnormalities or other evaluations (e.g., vital signs) detected during the  
607 trial, or present at the time of signing the informed consent and worsening after  
608 the trial begins, will only be recorded as specified in this protocol if they are  
609 considered clinically significant by the investigator or related to the investigational  
610 medication.

#### 611 **15.6. SAE Reporting Procedure**

612 Investigators must immediately notify the Principal Investigator (always within 24  
613 hours of becoming aware) of all SAEs using the designated form (SAE Reporting  
614 Form).

## **16. STATISTICAL ANALYSIS**

### **16.1. DESCRIPTION OF THE STATISTICAL ANALYSIS**

All statistical analysis will be performed by intention-to-treat. The safety analysis will include all patients who have received at least one dose of treatment or one cycle of TMS.

For the analysis of normality and equality of variances of continuous variables, the Shapiro-Wilk test and Levene's test will be used, respectively. Quantitative variables will be presented as mean and standard deviation and will be compared using the Student's t-test or non-parametric test where appropriate. Qualitative variables will be expressed as frequency and percentage and compared using the  $\chi^2$  test and Fisher's exact test when at least 25% of the cells in the contingency table show an absolute frequency of less than 5.

The primary analysis will be the difference in brain metabolism in the region of interest involved in the disease between the two treatment arms at 6 months. A statistical analysis will be used with a p-value <0.05 (two-tailed). The same analysis will be used to evaluate the change in the secondary outcomes of the study.

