In recent years, the potential utility of non-invasive neuromodulation therapies, particularly transcranial direct current stimulation (tDCS) and transcranial magnetic stimulation (TMS), has been explored in neurodegenerative diseases (Dong et al., 2020), and specifically in PPA (Norise & Hamilton, 2017; Nissim et al., 2020). Transcranial magnetic stimulation (TMS) is a technique based on the principle of electromagnetic induction to create an electric field in the brain. It is used as a non-invasive treatment for different conditions, such as depression, bipolar disorder, Parkinson's disease, epilepsy, and post-stroke aphasia rehabilitation.

Initial studies demonstrated that repetitive transcranial magnetic stimulation (rTMS) and/or transcranial direct current stimulation (tDCS) improved naming abilities in patients with Alzheimer's disease (Cotelli et al., 2006) and in patients with nvPPA (Finocchiato et al., 2006; Cotelli et al., 2012; Trebastoni et al., 2013; Cotelli et al., 2014; Gervits et al., 2016) and svPPA (Teichmann et al., 2016).

Over the past four years, several studies have been published, most of which focus on transcranial direct current stimulation (Cotelli et al., 2020). Notably, the largest sample size study was conducted by Tsapkini and collaborators (2018), who randomized 36 patients with PPA to receive either tDCS (targeting the left inferior frontal gyrus) combined with speech therapy or sham tDCS combined with speech therapy. This was a crossover study involving 15 consecutive sessions over 3 weeks, followed by a 2-month washout period. The intervention showed favorable results for the treatment group, with benefits observed both in the trained items targeted by the speech therapy and in untrained items. The effect was especially beneficial for the non-fluent and logopenic variants. Subsequent

85 analyses of this trial revealed changes in brain connectivity (de Aguiar et al., 2020;  
86 Tao et al., 2021).

87

| Table 1. tDCS studies in PPA (excluding studies with 5 or fewer patients and sub-studies of the main trial). |                               |           |                                                                             |              |              |             |                                                                             |

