## **6. DESCRIPTION OF THE TREATMENT**

There will be two treatment arms:

1. Active TMS + speech therapy
2. Sham TMS + speech therapy

Patients will be randomized in a 2:1 ratio, stratified by PPA variant (non-fluent, semantic, logopenic).

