### **15.2. SAMPLE SIZE CALCULATION**

The sample size calculation was based on the primary endpoint. In a sample of 70 patients with PPA who were longitudinally evaluated with two FDG-PET studies, the rate of decline in brain metabolism in a region of interest covering a large part of the left hemisphere follows a linear regression:  $y = 74.82 + 15.16 * \text{number of months}$ . This indicates a reduction in brain metabolism at 6 months of 167.78 (122–206). Assuming that the treatment could reduce this decline in brain metabolism by at least 20%, the estimated required sample size is 54 participants. Considering a 10% dropout rate, the final sample size was established as 60 participants.

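### Section 16.1 chooses between Student's t-test and a rank test after looking at the data, and neither allows for unequal variances under 2:1 allocation; one prespecified unequal-variance analysis is a cheap improvement

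*Protocol*

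**What the plan says.** Section 16.1 of the protocol opens its account of continuous variables with preliminary tests: for normality and equal variances, "the Shapiro-Wilk test and Levene's test will be used, respectively". Quantitative variables then "will be compared using the Student's t-test or non-parametric test where appropriate". The section gives no significance level for the preliminary tests, does not say which result leads to which test, and does not name the non-parametric test.

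The sentence on the primary outcome, which places the comparison at month 6 and is followed by a two-tailed 0.05 threshold, reads "The primary analysis will be the difference in brain metabolism in the region of interest involved in the disease between the two treatment arms". It names no test, so the general sentence is the only rule in the document for the primary comparison. Section 16.1 extends the same analysis to the secondary outcomes.

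Two other places bear on this. Section 6 states "Patients will be randomized in a 2:1 ratio". The sample size section (numbered 15.2, within section 16) rests on a difference in mean decline: "Assuming that the treatment could reduce this decline in brain metabolism by at least 20" per cent.

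**The concern.** Student's t-test pools the variances of the two arms. With equal arms, unequal variances do little harm. With 2:1 arms, the pooled standard error is too large when the larger arm is the more variable, and too small when the smaller arm is. A Mann-Whitney test does not cure this, because its null distribution also assumes that the two arms share one distribution. If Levene's test flags unequal variances, section 16.1 therefore names no test built for that condition.

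Two further things are at stake. At this sample size Levene's test misses most moderate differences in spread, so it protects little. And the two tests answer different questions. Unless the arms differ by a pure shift, a rank comparison does not in general estimate the difference in mean decline that the sample size assumes, so what the primary result means would depend on the data.

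**Working it through.** **The plan's own figures.** 54 / (1 − 0.10) = 60, as stated. Under 2:1, 54 evaluable patients are 36:18 and 60 randomized are 40:20 (active listed first, so read as active:sham). The target difference is 0.20 × 167.78 = 33.6 units. The stated regression gives 74.82 + 15.16 × 6 = 165.78, hence 33.2; that mismatch is a separate matter and changes nothing here. The 54 cannot be reproduced, because neither an SD nor a power is stated. Assuming 80% power and two-sided 5%, it implies SD = 33.56 / [(1.96 + 0.8416) × √(1/36 + 1/18)] = 33.56 / 0.809 = 41.5, or 41.0 with 33.16.

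**Assumptions.** The SD ratio between arms is not in the documents. The preliminary tests are taken at 0.05, and any failure (Shapiro-Wilk in either arm, or Levene) leads to Mann-Whitney; otherwise pooled t.

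**Bias of the pooled standard error at 36:18.** With s_a and s_s the active and sham SDs:

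pooled/true = √{ [(35 s_a² + 17 s_s²)/52 × (1/36 + 1/18)] / [s_a²/36 + s_s²/18] }

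- Active SD 1.25 times sham: √[(1.3786 × 0.08333) / 0.09896] = 1.077, about 8% too large.
- Sham SD 1.25 times active: √[(1.1839 × 0.08333) / 0.11458] = 0.928, about 7% too small.

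**Simulated two-sided error at 36:18** (normal data, equal means; 20,000 trials per cell for ratios 0.67, 1 and 1.5, simulation standard error about 0.15 points):

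| SD ratio active/sham | Pooled t | Mann-Whitney | Two-stage rule | Welch |
|---|---|---|---|---|
| 0.67 | 8.1% | 6.6% | 7.1% | 4.8% |
| Sham 1.25 times active | – | – | about 6.7% | about 5% |
| 1 | 5.2% | 4.8% | 5.2% | 5.2% |
| Active 1.25 times sham | – | – | about 3.9% | about 5% |
| 1.5 | 2.4% | 3.2% | 2.9% | 4.6% |

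Repeated runs at 1.25 gave 6.7–6.8% and 3.7–3.9%. With equal arms of 27:27, the pooled t stays at 4.8–5.2% for SD ratios from 0.5 to 2, so the distortion comes mainly from the 2:1 ratio. Levene's test detects a ratio of 1.25 in only 13–18% of trials.

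**Equal variances.** At the difference giving nominal 80% power: pooled t 78.3%, two-stage rule 77.8%, Welch 77.2%. The rule does no harm here, and Welch costs about 1 point against the pooled t.

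**What ratio do the documents suggest?** The only pointer is section 2, on an earlier tDCS trial: "The effect was especially beneficial for the non-fluent and logopenic variants". Table 1 gives that trial 10 semantic-variant patients among 36. Suppose, as an extreme, that the semantic variant gains nothing and the others carry the whole mean benefit of 33.6:

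- Effect in the others: 33.6 × 36/26 = 46.5.
- SD of the effect across patients: 46.5 × √(10/36 × 26/36) = 20.8.
- Active/sham SD ratio: √(41² + 20.8²) / 41 = 1.12.

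Simulating that mixture at 36:18 gives power of 74.4–74.5% for the two-stage rule and 76.1–76.6% for Welch, a loss of about 2 points. At a ratio of 1.12 with equal means, the rule's error is 4.5%.

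**The case against.** **The branch rule is a reading.** Levene's test is often run beside a t-test to choose between the pooled and unequal-variance forms, and the words on appropriateness could be stretched to cover that. The text does not say so, and that reading lessens the problem without removing it: at ratios 0.67 and 1.5 the error is 6.6% and 3.7%, against 7.1% and 2.9%. A SAP, not shown, may fix the test. But the protocol does more than leave the choice open: it states a data-driven procedure, which should be corrected in either case.

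**The size is easy to overstate.** A reader might infer that neither test is valid in this trial and that 5% is lost whatever happens. The documents do not support that. If the treatment affects nobody, the arms share one distribution and both tests are valid; the error figures concern equal means with unequal spread. A reader might also infer a large power loss from a ratio such as 1.5. With an SD of 41 that needs patient-level effects with an SD of about 41 × √(1.5² − 1) = 46, larger than the mean effect itself, and nothing in the protocol points there. The inflated-error direction, with the sham arm more variable, has no documentary basis. Even the 1.12 borrows from a crossover trial of a different stimulation technique, site, duration and outcome.

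**Chance switching.** With every assumption true, the preliminary tests still trip in about 14% of trials. A reader might infer that one trial in seven then changes what it estimates. It does not: with normal data and equal variances, the rank test's shift parameter is the mean difference, and error and power are almost unchanged.

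**Overlap with covariate adjustment.** A model with variant and its interaction with treatment would absorb spread due to variant. Adding baseline or variant alone would neither supply an unequal-variance standard error nor remove the data-driven choice.

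**Conclusion.** The point stands as a minor one. Section 16.1 fixes a data-driven choice between two tests, neither of which, on the ordinary reading, handles unequal variances under 2:1 allocation, and it is the only rule given for the primary outcome. The harm depends on an SD ratio that the documents do not give: practically none at 1, about 2 points of power at the ratio near 1.1 that the protocol's background could support, and an error of about 3.9% or 6.7% at an assumed 1.25, depending on which arm varies more. Separately, where data are not normal or variances differ, switching to ranks means that the primary result in general no longer estimates the difference in mean decline used for the sample size. These figures rest on 36:18 evaluable patients, normal data, preliminary tests at 0.05 and Mann-Whitney as the rank test.

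**What to change.** In section 16.1, remove the Shapiro-Wilk and Levene tests as a means of choosing the test for outcome comparisons. Prespecify one analysis for the primary and secondary continuous outcomes: the between-arm difference in mean change from baseline, with an unequal-variance standard error and 95% CI. Use Welch's test, or a heteroscedasticity-robust standard error if covariates are in the model. Keep the rank test as a named sensitivity analysis, and carry the same wording into the SAP.

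The cost is a sentence or two of text and about 1 point of power against the pooled t-test if the variances are in fact equal (77.2% against 78.3%). No change to sample size, visits or data collection is needed.

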## **4. STUDY OUTCOMES**

### **4.1. Primary outcome**

To compare the effect of TMS and speech therapy with speech therapy and sham TMS on the progression of primary progressive aphasia, as determined by brain metabolism on FDG-PET at 6 months.

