## 516 **14. EFFICACY OUTCOMES**

- 517 **● Primary outcome**

518 The primary variable of the study for the assessment of efficacy is the change in  
519 regional cerebral metabolism between the baseline and final visits.

520       • **Secondary outcomes**

521 MLSE

522 Trained Word Naming

523 Spontaneous Speech: number of words per minute

524 Activities of Daily Living: IDDD

525 Neuropsychiatric Symptoms: NPI

526 Adverse events related to treatments during the 6 months following  
527 randomization.

528 **15. SAFETY MEASURES AND RISK MANAGEMENT**

529 It is the responsibility of the investigator to detect and document any event that  
530 meets the criteria and definitions of an adverse event or serious adverse event as  
531 established in this protocol. Safety assessments will be conducted in accordance  
532 with Good Clinical Practice guidelines and current legislation. Adverse effects will  
533 be recorded during each study visit. The analysis will include the type of adverse  
534 effect and its frequency.

535 **15.1. Definitions**

536 **15.1.1. Adverse Event (AE)**

537 Any harmful health incident in a patient or clinical trial subject treated with a  
538 medication, regardless of whether there is a causal relationship with the  
539 treatment. An AE can therefore be any unfavorable and unintended sign (including  
540 an abnormal laboratory finding), symptom, or disease temporally associated with  
541 the use of an investigational drug, whether or not it is related to the drug.

542 **15.1.2. Adverse Reaction (AR)**

543 Any harmful and unintended reaction to an investigational drug, regardless of the  
544 dose administered. In this case, there is a suspected causal relationship between  
545 the investigational drug and the adverse event.

546 **15.1.3. Serious Adverse Event (SAE) and Serious Adverse Reaction (SAR)**

547 Any adverse event or adverse reaction that, at any dose: results in death, is life-  
548 threatening, requires hospitalization or prolongs an existing hospitalization,

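### The primary endpoint is worded as change from baseline in section 14 and as metabolism at 6 months in sections 4.1 and 16.1; one primary analysis should be fixed, preferably adjusted for baseline uptake

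*Protocol*

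**What the plan says.** The protocol describes the primary endpoint in four places.

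- **Section 14 (efficacy outcomes):** "The primary variable of the study for the assessment of efficacy is the change in" "regional cerebral metabolism between the baseline and final visits". This is a change score.
- **Sample size section (numbered 15.2, placed under section 16):** the target is also a change: "Assuming that the treatment could reduce this decline in brain metabolism by at least 20" per cent. The decline in question is put at 167.78 units over 6 months.
- **Section 4.1 (primary outcome):** progression is to be judged "as determined by brain metabolism on FDG-PET at 6 months", with no mention of baseline.
- **Section 16.1 (statistical analysis):** the primary analysis is the "difference in brain metabolism in the region of interest involved in the disease between the two treatment arms at 6 months", again with no mention of baseline or change.

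The primary-analysis paragraph of 16.1 names no test. The general paragraph before it says that quantitative variables "will be compared using the Student's t-test or non-parametric test where appropriate". The primary-analysis paragraph then closes with: "The same analysis will be used to evaluate the change in the secondary outcomes of the study".

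**The concern.** Change from baseline and level at 6 months are different outcome variables. Randomisation makes the expected between-arm difference the same for both, but their variances differ and so may the result in any one data set. The level carries all the stable between-patient variation in regional uptake, plus any chance baseline imbalance between a larger and a smaller arm. The change score removes the stable part but adds the measurement noise of a second scan.

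The sample size is argued on change. If 16.1 is carried out as worded, the trial runs an analysis whose power was never considered. While both wordings stand, two primary analyses can each be defended from the protocol, and a SAP that adopts either one contradicts part of it.

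**Working it through.** **Inputs from the protocol.** Two-sided alpha 0.05 (16.1); 54 evaluable patients, raised to 60 for 10% dropout; decline of 167.78 units at 6 months; 20% reduction; 2:1 allocation (section 6), so 54 patients split 36 to 18.

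**Reproducing the plan's figures.** Dropout reproduces: 54 / 0.9 = 60. The target difference is 0.20 × 167.78 = 33.56 units. The 54 itself cannot be reproduced uniquely, because neither power nor SD is stated. (The quoted regression gives 74.82 + 15.16 × 6 = 165.78 rather than 167.78. That would make the target 33.16 and barely affects what follows.)

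**Assumptions needed.** Power on change is taken as 80%. The standard error factor is √(1/36 + 1/18) = 0.2887. With the noncentral t on 52 degrees of freedom, an SD of change of 40.7 gives 80% power for 33.56 (SE = 40.7 × 0.2887 = 11.75). The variance of uptake, s², is taken as equal at both visits, and ρ is the correlation between baseline and 6-month uptake.

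**Formulas.**

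- Change score: variance 2s²(1 − ρ)
- 6-month level, unadjusted: variance s²
- Level or change adjusted for baseline (ANCOVA): variance s²(1 − ρ²)

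Holding the SD of change at 40.7 gives s = 40.7 / √(2(1 − ρ)). For example, at ρ = 0.8, s = 40.7 / √0.4 = 64.4 and the ANCOVA SD is 64.4 × √0.36 = 38.6.

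| ρ | SD of level | Power, change | Power, 6-month level | Power, ANCOVA |
|---|---|---|---|---|
| 0.5 | 40.7 | 80% | 80% | 90% |
| 0.6 | 45.5 | 80% | 71% | 88% |
| 0.7 | 52.5 | 80% | 58% | 86% |
| 0.8 | 64.4 | 80% | 43% | 84% |
| 0.9 | 91.0 | 80% | 24% | 82% |

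At ρ = 0.5 the level and change analyses are equally powerful. Below 0.5 the level is the better of the two: 91% at ρ = 0.3. The level analysis falls under 40%, half of the assumed 80%, only above ρ of about 0.81. If the planned power was 90%, the level analysis has 90%, 71%, 54% and 31% at ρ = 0.5, 0.7, 0.8 and 0.9.

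**Patients needed, level against change.** The ratio is 1 / (2(1 − ρ)): 1.0, 1.25, 1.7, 2.5 and 5.0 down the table.

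**Baseline imbalance.** At ρ = 0.8 the chance difference between arms in mean baseline uptake has an SD of 64.4 × 0.2887 = 18.6 units, against a target effect of 33.56. A t-test on the 6-month level does not correct for it.

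**Why the adjusted model settles both wordings.** Relative to change, the ANCOVA variance is (1 − ρ²) / (2(1 − ρ)) = (1 + ρ)/2. Relative to the level it is 1 − ρ². Neither ratio exceeds 1. With baseline in the model, regressing the 6-month value or the change on arm gives the same treatment coefficient, because the two outcomes differ only by the covariate.

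**The case against.** The strongest reply is that the protocol, read as a whole, points to change. Section 14 says so outright, the sample size section claims to rest on the primary endpoint and uses decline, the hypothesis and section 4.1 speak of progression, and in 4.1 and 16.1 the phrase about 6 months may only name the time point. The closing sentence of the primary-analysis paragraph applies the same analysis to change in the secondary outcomes, which suggests that the primary analysis is also of change. This largely stands: the text is ambiguous and does not firmly commit to the raw level. It does not remove the problem. The sentence that fixes the primary analysis omits change, and section 4.2 words every numbered secondary outcome at 6 months, so the ambiguity reaches those outcomes too.

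It is also fair that the t-test stands in a general paragraph and is not tied by name to the primary analysis, and that covariates may be set out in a SAP that is not shown. The lack of ANCOVA is therefore not an error in itself, and a change-score comparison would be valid and match the sample size.

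Finally, a reader might infer that analysing the 6-month level would lose most of the planned power. The documents do not support that. They state no SD, no power and no correlation, and the result runs from a gain below ρ = 0.5 to a large loss at 0.9. High correlation is plausible for repeated uptake in one region, but it is an assumption.

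**Conclusion.** The inconsistency is real and lies within the protocol: section 14 and the sample size use change, while the literal wording of 4.1 and 16.1 is metabolism at 6 months. Its cost depends on a correlation that the protocol does not give. Under the working's assumptions, the literal reading costs nothing against change at a correlation of 0.5, 22 percentage points at 0.7 (80% to 58%) and 56 points at 0.9 (80% to 24%). A baseline-adjusted analysis keeps 82% to 90% over the same range. The need to reconcile the wording does not depend on any of these figures. The preference for the adjusted form rests on its being at least as precise as either reading, for one degree of freedom.

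**What to change.** State one primary analysis in identical terms in sections 4.1, 14 and 16.1: the between-arm difference in change in region-of-interest uptake from baseline to 6 months (equivalently, in the 6-month value), estimated from a linear model with treatment arm and baseline uptake as terms, and reported with its 95% confidence interval. Use the same form for the secondary outcomes that have a baseline value (MLSE, trained word naming, words per minute, IDDD, NPI), each with its own baseline, and align section 4.2 accordingly.

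If the sponsor prefers an unadjusted comparison of change scores, saying so in all three sections would also remove the contradiction.

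The cost is protocol wording and one degree of freedom. No new data are needed, since a baseline FDG-PET is already scheduled for every patient. The change should be made before any unblinded data are seen.
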